## Abstract

**Background:**

Chronic stress is detrimental to health, and children and young people have had to cope with significantly more stress since the start of the COVID-19 pandemic. In particular, stress at school and in relation to learning is a major problem in this age group. Studies in Germany have indicated that the pandemic has led to a reduced quality of life (QoL) and an increased risk for psychiatric disorders in children and adolescents. Schools are an ideal setting for interventions against stress, which is one of the strongest predictors for the development of psychosocial problems. The present study seeks to address stress by means of a short prevention training programme in schools, including emotion regulation, mindfulness, and self-compassion. In addition to information material for self-study, students should have the opportunity to actively deal with the topic of stress and develop coping strategies within a short space of time. In contrast to very long stress reduction programmes that often last several weeks, the programme is delivered in just 90 min.

**Methods:**

The effectiveness of the short and economical prevention programme *LessStress* will be examined in a cluster-randomised controlled trial (RCT) encompassing 1894 students. At several measurement time points, students from two groups (intervention and control) will be asked about their subjectively perceived stress levels, among other aspects. Due to the clustered nature of the data, mainly multilevel analyses will be performed.

**Discussion:**

In Germany, there are no nationwide universal prevention programmes for students against stress in schools, and this gap has become more evident since the outbreak of the pandemic. Universal stress prevention in schools may be a starting point to promote resilience. By dealing with stress in a healthy way, mental health can be strengthened and maintained. Moreover, to reach at-risk students at an early stage, we advocate for a stronger networking between child psychiatry and schools.

**Trial registration:**

German Clinical Trials Register (DRKS) DRKS00025721. Registered on November 4, 2021

## Administrative information

Note: the numbers in curly brackets in this protocol refer to SPIRIT checklist item numbers. The order of the items has been modified to group similar items (see http://www.equator-network.org/reporting-guidelines/spirit-2013-statement-defining-standard-protocol-items-for-clinical-trials/).

## Introduction

### Background and rationale {6a}

#### Background

The negative impact of the SARS-Cov2 pandemic on adolescents’ mental health and QoL is becoming increasingly apparent. Recent studies in Germany and Austria have revealed an alarming decrease in QoL and an increase in the risk of developing psychiatric disorders among children and adolescents [1, 2]. School is the natural environment for cognitive and social learning in young people, but several lockdowns and school closures over the past pandemic school years have exerted a strong impact on students’ learning: Learning goals have generally not been reached, and students from disadvantaged backgrounds have been especially impacted [3, 4]. The digitalisation of education had been rather hesitant prior to the pandemic, and it remains an enormous challenge for schools, teachers, students, and their parents [5]. It is clear that the past 2 years have led to increased stress for young people, which must be surmounted given the students’ increasing knowledge gaps.

One extremely important conclusion that can be drawn from the ongoing pandemic situation is that children and young people are suffering [6–8] due, among other factors, to adverse home conditions, family stress, or mental illness. Therefore, it is essential to provide rapid assistance and to develop and evaluate effective, efficient prevention programmes that are easy to access and implement [6]. As child and adolescent mental health is hugely multifaceted [7], we limit ourselves here to one risk factor of which we are all aware, and with which students have struggled a great deal over the last 2 years: stress [1, 2]. A very broad definition of stress goes back to Hans Selye, a twentieth-century physician, biochemist, and hormone researcher, who said “Stress is the nonspecific response of the body to any demand” [9]. There are many different definitions of stress depending on the context. In the behavioural sciences, stress describes the perception of a threat, which is reacted to with anxiety, emotional tension, and discomfort. Neuroendocrinological stress can be described as a reaction of the body, more precisely the sympathetic nervous system, to release ACTH and adrenal glucocorticoids in response to a stimulus [10]. In the psychological context, it is assumed that the induction of negative affective states (e.g. feelings of anxiety and depression) influences the pathogenesis of physical illnesses [11]. Chronic stress is likely to result in long-term or lasting changes in emotional, physiological, and behavioural responses, which in turn affect susceptibility to and progression of disease, including stressful events such as trauma [12]. The endocrine response triggered by stress is composed of two endocrine response systems that are particularly responsive to psychological stress: the hypothalamic-pituitary-adrenal (HPA) axis and the sympathetic-adrenal medulla (SAM) system [13, 14]. Cortisol as the primary effector regulates a wide range of physiological processes. The repeated and prolonged activation of the HPA and SAM systems can severely impair physiology and is therefore at increased risk for physical and psychiatric disorders [11]. Symptoms associated with stress include loss of appetite, headache, stomach pain, difficulty concentrating, sleep disorders [15], and a decrease in QoL [16]. Stress is perceived differently from person to person, has a cumulative effect, and is seen as one of the strongest predictors of mental illness [15, 17]. A survey of around 230,000 6–18-year-olds conducted by the Kaufmännische Krankenkasse in 2017 [18] revealed a significant increase in mental disorders among children and adolescents with stress being identified as the major issue. Another prospective cohort study reported depression or neurotic and somatoform disorders to be the main disorders comorbid to stress [19]. This finding is supported by a body of evidence conducted in other studies [20–22]. The increased stress in young people pertains not only to school and academic achievement, but also to further factors such as stress with parents (regarding both school and home life), overstimulation by media, bullying in social networks, or general fears, which all contribute to a higher stress perception. School and school-related stress is certainly a major concern, even in elementary school: Young children are vulnerable to stress and show stress symptoms, and it has been identified that girls are more susceptible to stress and are coping differently compared to boys [20, 23]. Stress levels among children and adolescents appear to be higher in more academic school types than in vocational schools [24], and rise during adolescence [25]. With respect to school, and specifically stress caused in school, it is necessary to address and prevent anxiety (separation anxiety, fear of school, social anxiety, and test anxiety) together with the students themselves [26]. Crucially, moreover, stress leads to neurocognitive alterations [27].

But is stress prevention effective and feasible? In a recent study examining the mediating effects of mental and physical health problems on health care costs in a sample of German school (*N* = 284, *M* = 16.75 ± 0.64 years), Eppelmann and colleagues found that adolescents’ perceived stress had a significant effect on overall health care costs. An increase of stress by 1 *SD* increased the chances for costs by an odds ratio of 1.39. This effect was fully mediated by mental health (problems) [28]. Mental illnesses are the second largest cost drivers in the German health system [28, 29].

Prevention research has yielded mixed findings regarding school programmes targeting stress (stress management, coping skills, mindfulness/awareness, relaxation, life skills training): While meta-analyses have found some to be effective [30, 31], other meta-analyses have shown different results [32, 33]. However, due to methodological limitations within these reviews, more research is necessary. So far, the meta-analyses in this area have led to the following major conclusions:The tested programmes were quite long (up to 50 min per session over several weeks, 8–30 sessions)The frequency of sessions was very high (just 10 min per session but implemented several times a day, or up to 42 times)Sample sizes were very low (21 to 323)Follow-ups were often missingMeasurement of stress symptoms was not incorporatedNot aimed at adolescents of middle-school ageLack of internal consistency for the applied measuresIt may be necessary to integrate parents into stress prevention programmes

In sum, while children and adolescents did gain more knowledge about stress and coping with stress, the programmes did not reduce self-perceived stress. One approach is mindfulness at school, which has become highly popular in the USA and the UK, where there are even mindfulness-based apps for teachers and students [34]. A recent stress prevention programme for German students (3× 45 min) revealed significant effects in terms of knowledge gains but no reduction in self-perceived stress between the control and intervention groups, although the students did like the programme and would recommend it [35]. The authors stated that in contrast to their prevention programme, other interventions such as mindfulness-based stress reduction (MBSR) [36], when executed more than 20 times, or a programme lasting for 10 units [37], were effective in stress reduction. They concluded that in order to acquire individual stress coping models, students need more time to generalise to their own situation. At this point, the following question arises: How do the effectiveness, required effort, and practicability of a programme relate to one another? For example, what can we achieve with a combination of psychoeducation and group work? With *LessStress*, we take the approach of conveying knowledge about stress by means of a booklet and targeting stress-coping strategies through one training unit.

#### Reason for the trial

The COVID-19 pandemic has made the urgent need for stress prevention in adolescence even more apparent. In the field of prevention research, there have long been calls for more, and especially effective programmes for children and adolescents [38], given the frequent onset of mental disorders in adolescence, the persistence of the disorders, and a particular vulnerability in this age group [39, 40]. We are currently faced with a situation of many children and adolescents with high levels of stress, especially concerning school [18, 41]. Life during the pandemic has significantly exacerbated stressful situations at home and at school. Meta-analyses have demonstrated the effectiveness of stress prevention programmes at schools, but due to the acute nature of the situation, we need to evaluate short, easy-to-implement, and cost-effective programmes [38, 42–45]. *LessStress* differs from the programmes that have been developed and evaluated so far: It saves time and money, is easy to implement in schools, and combines different approaches such as skills-based methods, mindfulness, and preventive measures. In view of the high levels of self-perceived stress among children and adolescents, with the pandemic multiplying the challenges at school, effective prevention is essential.

## Objectives {7}

### Research hypothesis

The universal prevention program *LessStress* reduces students’ subjective stress experience and can thus help to maintain or strengthen their mental health.

### Objectives

In order to find out whether the universal prevention programme *LessStress* has a significant impact on students’ subjective experience of stress, the intervention group (IG) will be compared with a waiting list control group (WL) in terms of scores on the *Perceived Stress Scale 10* (PSS-10) [46, 47].

We expect that students who take part in the universal prevention programme *LessStress* will significantly benefit, as measured by the primary and secondary outcomes. Given the preventive nature of the programme, we expect to find a decrease in self-perceived stress and fewer mental health problems in the IG after 6 months, which will be assessed with the secondary outcomes.

To test the efficacy, we will collect data using self-administrated questionnaires, which will be implemented within an online survey. The questionnaires are standard instruments in the field of psychology and show good psychometrics properties. Questionnaires remain the means of choice to assess personal states and feelings.

#### Primary objectives

Self-perceived stress will be assessed using the German 10-item version of the *Perceived Stress Scale* (PSS-10) [47]. We expect a significant decrease for the primary outcome “self-perceived stress” in the IG.

#### Secondary objectives

In addition to the primary outcome, the evaluation of *LessStress* will include the following secondary outcomes: emotion regulation, self-compassion, sleep quality, depression index, anxiety index, self-injurious behaviour, eating disorder symptoms, and health-related quality of life. To investigate adolescents’ resources, we will assess protective and resilience factors (see Table 1 for further details).

**Table 1 Tab1:** Overview of the questionnaires being used

**Instrument**	**Content**	**Length**
**PSS-10:** *Perceived Stress Scale* (primary outcome measure)	Primary objective Developed by Cohen, Kamarck, and Mermelstein, translated and validated by Klein, Brähler et al., 2016 [47]. Investigates the degree to which life was unpredictable, uncontrollable, and overwhelming within the last month. Very good internal consistency (*a* = .84). Positive correlation with depression and anxiety, negative one with quality of life.	10 items
**DERS-SF***: Difficulties in Emotion Regulation Scale Short Form*	Measures emotion (dys-)regulation multidimensional. According to the model by Gratz and Roemer [48], the subscales “non-acceptance”, “problems with target oriented behaviour”, “impulsive conduct problems”, “lack of emotional awareness”, “limited access to emotion regulation strategies”, and “lack of emotional clarity”.	16 items
**SCS:** *Self-Compassion Scale*	The Self-Compassion Scale was developed by Neff in 2003 with 26 items. The shortened version showed satisfactory to good psychometric properties so far [49].	12 items
**WHO-5***: WHO Fragebogen zum Wohlbefinden*	The facets of psychological well-being like mood, interest, energy, and drive within the last 2 weeks are assessed. Used worldwide, non-invasive questions, translated in 30 languages, the first version was published in 1998. Very good internal consistency with *α* = .85. German version by Allgaier [50].	5 items
**PHQ-4***: Gesundheitsfragebogen für Patienten – Depressionsmodul*	The PHQ-4 is a valid screening instrument for symptoms of depression and anxiety symptoms (Cronbach α >0.80) [51]. Responses are scored as 0 (“not at all”), 1 (“several days”), 2 (“more than half the days”), or 3 (“nearly every day”). PHQ–4 scores go from normal (0 –2) to mild (3–5) to moderate (6–8) to severe (9 –12). Symptoms within the last 2 weeks are being interrogated.	4 items
**DSHI-9***: Deliberate Self-Harm Inventory*	An initial question is asked whether someone has already intentionally injured his-/herself. If this is answered with yes, the type, onset, and frequency of self-harm are obtained [52].	1–6 items
**ISI***: Insomnia Severity Index*	Measures the quality of sleep and goes back to [53]. Difficulties falling asleep or staying asleep and the impairment they cause in everyday life are in the focus.	7 items
**SEED***: Short Evaluation of Eating Disorders*	It obtains the central symptoms of anorexia (underweight, fear of weight gain, impaired body awareness) and bulimia (binge eating, compensatory measures, excessive preoccupation with figure and weight) within the last month [54]. It has already been used in student samples with good experience.	6 items
**SFF***: Schutzfaktoren*	This short questionnaire captures three scales of protective factors that correlate significantly with data from the SDQ. Children who have more social, personal, and family resources are correspondingly less conspicuous in the SDQ [55].	12 items
**SISE:** *Single-Item Self-Esteem Scale*	This 1-item version goes back to the 10-item scale of the Rosenberg Self-Esteem Scale (RSES) developed by Rosenberg in 1965. The original sheet captured self-esteem with 5 positive and 5 negative questions. Recent studies have also demonstrated very good measurement properties for the 1-item version [56]. The question asks how well the statement “I have high self-esteem” applies to oneself. A 4-point Likert scale is then presented.	1 item
**CD-RISC-10:** *Connor-Davidson Resilience Scale-short form*	The long version was designed by Connor-Davidson in 2003 to measure resilience. Resilience means the ability to cope with internal or external stressors. The CD-RISC is widely used and has good psychometric properties (*a* = .84) [57]	10 items
**FAS III:** *Family Affluence Scale*	The FAS III measures the socioeconomic status using 6 questions and has very good quality criteria. Furthermore, the MacArthur scale question is connected, which asks about the subjective assessment of the prosperity of the adolescents’ own family [58]	6 items + 1

Finally, we will record demographic variables (e.g. age, gender) and socioeconomic status.

### Aims

The study will be carried out with 1894 adolescents at different schools in the Federal states of Bavaria, Mecklenburg Western Pomerania, and Hesse and encompasses the following aims:Improving stress managing skills in studentsEnhancing students’ quality of life and their mental health

## Trial design {8}

The *LessStress* trial is designed as a cluster-randomised, controlled, non-blinded superiority trial with two parallel groups and a primary endpoint of self-perceived stress after 6 months. We will perform a random assignment on the school level with a 1:1 allocation ratio. The study will last for 6 months and will include four measurement time points: Pre = baseline, Post = student and teacher evaluation, T2 = 3-month follow-up, and T3 = 6-month follow-up (Fig. 1).

**Fig. 1 Fig1:**
[figure not shown]
Timetable for the study *LessStress*

### Randomisation

Randomisation will be performed at the school level in order to avoid any interclass interference within the intervention and waiting list control group. To reduce bias, we will be supported by a co-worker of the clinic ([name]), who is not involved in this project and a member of another working group (Cognitive and computational Neuroscience), and will perform the randomisation using Microsoft Excel.

## Methods: participants, interventions, and outcomes

### Study setting {9}

The study will be conducted in the Federal states of Mecklenburg-West Pomerania, Bavaria, and Hesse [59]. Due to the broad geographical sample and the wide age range of 12–18 years, we will be able to obtain a well-generalisable epidemiological overview. The number of participating schools or classes cannot be predicted at this stage, for the following two reasons: (1) the pandemic has dramatically increased the stress and workload in schools, which is associated with less participation in non-school projects. (2) We are focusing on direct contact with teachers, school psychologists, and school social workers to bring the program to their schools, which can lead to more time required for recruitment.

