### Eligibility criteria {10}

#### Inclusion and exclusion criteria

Participants must be aged between 12 and 18 years and be in the 6th to 12th grade. We chose this age group for two reasons: (1) The onset of adolescence brings about a clear increase in social, cognitive, and emotional challenges and expectations. Furthermore, neurological and cognitive change processes are underway [60]. Taken together, this can correspondingly increase self-perceived stress. (2) Epidemiological data show that the end of childhood, the beginning of adolescence, and adolescence itself represent the period with the highest risk of onset of mental disorders [28, 61].

Only one exclusion criterion will be applied: lack of informed consent from the adolescents or their parents/guardians. Moreover, we will assess the presence of a psychiatric illness with accompanying psychotherapy in order to exclude these students from data analysis.

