### Who will take informed consent? {26a}

For the trial, the informed consent of the respective schools’ head teachers is required, as well as the informed consent of a legal guardian and of the students. If schools express an interest in participating, a meeting will be organised in order to provide detailed information about the study. In the case of participation, the legal guardians of students in the participating grades/classes will be given detailed written information sheets and will be able to watch an online presentation, in which the study is orally explained. The students will receive posters with information. If students wish to participate, they will provide their written consent by clicking on “Yes, I do want to participate in the study” on the first page of the online survey.

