### Sample size {14}

To analyse cluster-randomised trials, specific constraints must be followed, as individuals within a cluster are assumed to be more similar compared to individuals from different clusters. In order to detect significant effects, the sample size of the trial must be adjusted. This so-called clustering effect (1 + (*m*-1)×*p* [*m* = average number of subjects per cluster; *p* = intraclass correlation coefficient (ICC)]) resulted in an estimated *N* = 1795. For *m*, we assumed an average of 80 within an entire grade as the average class size in Germany varies nationwide (21.2–30.4 students per class), and the ICC was estimated quite conservatively at approximately 0.05 [70] on the basis of the primary outcome. Hence, a clustering effect of 4.95 was determined. Assuming a small effect size (Cohens *d* = 0.2) in universal prevention based on previous studies [71], with a significance level alpha = 0.05 and a power = 0.9, g*power suggests a total of *N* = 306 [72]. Considering the clustering effect, we have to multiply this by 4.95, reaching an overall *N* = 1515. Assuming a dropout rate of 25% due to moving out of the area, sickness, or other reasons, we must add another 379, leading to the final *N* = 1894.

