### Recruitment {15}

The recruitment will take place in autumn 2022. Schools are the most appropriate setting for universal prevention for the following reasons: (1) An adolescent’s life is mostly played out at school, (2) compulsory school attendance provides the opportunity to reach a large number of adolescents, and (3) there is evidence that students are more likely to accept such programmes within school than during their free time. The School Boards will help us to get in touch with eligible schools. *LessStress* targets classes from the 6th to 12th grade at public and private schools. Any school principal or council expressing an interest can officially register for potential participation via mail. In a next step, further information material regarding the study will be sent out if required. If schools agree to participate, a letter of consent has to be signed, stating how many grades and classes will participate in *LessStress*.

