### Interim analyses {21b}

Interim analyses are planned for baseline data collection. Epidemiological studies will be reported and, if appropriate, a comparison with data from another region will be explored. The study will automatically end with the last data collection in the last class after 6 months. Access to these interim results and the final decision on the termination of the study will be at the discretion of the study management (MK, AB, CS).

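### The claim of a generalisable epidemiological overview is not supported by a sample of volunteer schools from which students in psychotherapy for a psychiatric illness are excluded at analysis

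*Protocol article*

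**What the plan says.** Under Study setting, the protocol names the geographical spread and the age range of 12–18 as its reasons for expecting that "we will be able to obtain a well-generalisable epidemiological overview". Under Interim analyses, it plans to use the baseline wave in that way: "Epidemiological studies will be reported and, if appropriate, a comparison with data from another region will be explored".

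The route into the sample is described in three places:

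- Recruitment: "Any school principal or council expressing an interest can officially register for potential participation via mail". School Boards help to reach eligible schools, public and private schools are both targeted, and each school's consent letter states how many grades and classes will take part.
- Study setting: "We are focusing on direct contact with teachers, school psychologists, and school social workers to bring the program to their schools". The same paragraph says that the stress and workload the pandemic has brought to schools go with lower participation in outside projects.
- Informed consent: "the informed consent of the respective schools’ head teachers is required, as well as the informed consent of a legal guardian and of the students".

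The eligibility section has a single exclusion criterion, lack of consent. It then adds a rule about analysis: "we will assess the presence of a psychiatric illness with accompanying psychotherapy in order to exclude these students from data analysis". It does not say whether this rule covers the baseline reports.

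**The concern.** The generalisability statement is a positive claim, and the reasons given for it do not bear on it. Region and age range describe where the students come from. Whether results carry over to the student population depends on how schools and students were selected, and here selection is voluntary at every level. Some of it may be related to stress itself, since the protocol expects strained schools to take part less often.

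The exclusion of students in psychotherapy works against the same claim. An overview of stress, depressive and anxiety symptoms, self-injury and eating problems that leaves out students already in treatment describes a population from which some of the more affected members have probably been removed.

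What is at stake is the baseline report and any comparison with another region. A regional difference could reflect volunteering, grade, school type or the exclusion rule rather than region.

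**Working it through.** **Plan figure.** The protocol gives no figure for the baseline report. The nearest is the clustering factor under Sample size: 1 + (80 − 1) × 0.05 = 4.95, which reproduces. The point does not depend on it.

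**Step 1: does the reason given support the claim?**

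| Stage | What the protocol describes | Effect on representativeness |
|---|---|---|
| School enters | Own registration, or contact through school staff | No random selection described |
| Classes enter | The school states the number | Chosen within the school |
| Student enters | Head teacher, guardian and student all consent | Non-response at three levels |
| Student is analysed | Psychiatric illness with psychotherapy excluded | A defined group is missing |

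None of these stages is altered by covering three states or seven school grades. The protocol describes no sampling frame, quota or weighting. The size and direction of the bias from volunteering cannot be computed from the document.

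**Step 2: direction of the effect of the exclusion.** Let q be the share of students in psychotherapy for a psychiatric illness, pt the symptom frequency among them, and po the frequency among all others.

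- Frequency in all participants: q·pt + (1 − q)·po
- Frequency after the exclusion: po
- Shortfall: q·(pt − po)

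The shortfall is positive whenever pt exceeds po. It is zero if the two are equal, and it reverses if treated students have fewer symptoms.

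**Step 3: illustration of size.** The protocol gives none of q, pt or po. The ranges below are assumptions.

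| q | pt | po | All participants | After exclusion | Shortfall |
|---|---|---|---|---|---|
| 3% | 50% | 20% | 20.9% | 20% | 0.03 × 0.30 = 0.9 points |
| 3% | 80% | 15% | 16.95% | 15% | 0.03 × 0.65 = 1.95 points |
| 10% | 50% | 20% | 23% | 20% | 0.10 × 0.30 = 3.0 points |
| 10% | 80% | 15% | 21.5% | 15% | 0.10 × 0.65 = 6.5 points |

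**Step 4: regional comparison.** The protocol's own Background reports that stress differs between school types, rises during adolescence and affects girls more. An unstandardised contrast between regions would therefore carry differences in sex, grade and school type as well as any true regional difference.

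**The case against.** Voluntary schools and layered consent are normal in school trials and are not a design error. The trial exists for the comparison of the two groups on the PSS-10, and nothing here changes that comparison. The generalisability statement stands under Study setting and is not repeated where the baseline reports are planned. The protocol does not call its own results prevalences, and it hedges the regional comparison as something to explore if appropriate. All of this is fair, and it limits the weight of the point. It does not rescue the claim, which is written without qualification and is followed by a plan for epidemiological reports.

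Two stronger readings are tempting, and neither is supported.

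The first is that psychiatric cases in general are removed. The rule covers only students who have both a psychiatric illness and accompanying psychotherapy. Untreated cases stay in, and a comparison of healthy with clinically relevant students is planned among the subgroup analyses.

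The second is that the baseline figures will be too precise because clustering will be ignored. The arithmetic is simple. For an assumed frequency of 20% in 1894 students, the unadjusted 95% half-width is 1.96 × √(0.2 × 0.8 / 1894) = 1.8 points. Multiplied by √4.95 = 2.22, it becomes 4.0 points. But no section says that baseline figures will be computed without allowing for clustering. The statistical methods section says that the clustered structure must be taken into account, and its rule of using multilevel models only above an ICC of 0.1 is written for the group comparison. The inputs are borrowed as well: the ICC of 0.05 was set for the primary outcome, a 0–40 score, and the cluster size is a planning value ("we assumed an average of 80 within an entire grade"). The gap between 1.8 and 4.0 points therefore describes an analysis that nobody has planned.

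**Conclusion.** The point holds as a minor one. The design described does not have the generalisability the protocol claims, because the reasons offered do not address voluntary selection. As written, the exclusion of students in psychotherapy also reaches the baseline reports, or at least nothing exempts them.

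The exclusion would lower reported symptom frequencies on the assumption that treated students are more symptomatic than the rest. The direction is plausible. The range of about 1 to 6.5 points rests wholly on assumed inputs and is not evidence from this protocol. The bias from self-selected schools cannot be quantified, even in direction. The randomised comparison is untouched by this point.

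**What to change.** - **Study setting:** limit the statement to the participating schools and students, and drop the inference from region and age range.
- **Eligibility criteria and Interim analyses:** state that the psychotherapy exclusion does not apply to the baseline epidemiological report, or give that report with and without these students. The rule acts at analysis, and lack of consent is the only bar to entry, so no extra data collection should be needed.
- **Regional comparison:** label it as descriptive and standardise it for sex, grade and school type.
- **Good practice, not a correction of a stated error:** give school-clustered intervals for baseline estimates whatever the observed ICC.

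The cost is a few sentences and some additional tabulation. The downside is a weaker claim for the baseline report.
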